# Effectiveness of an mHealth Program on Reducing Blood Pressure Among Young Adults With Prehypertension: Protocol of a Pragmatic Cluster Randomized Controlled Trial

**DOI:** 10.2196/67216

**Published:** 2025-08-07

**Keywords:** prehypertension, hypertension, blood pressure, cardiology, cardiac, young adult, randomized controlled trial, mobile-based program, global health, mHealth, mobile health, mobile app, smartphone, digital health, digital intervention

## Abstract

**Background:**

The prevalence of prehypertension may be underreported because of its asymptomatic nature. This study will use a pragmatic mobile health (mHealth) app to deliver the intervention, which is expected to be well received by the young adult population.

**Objective:**

This study aims to assess the prevalence of prehypertension among young adults and evaluate the effectiveness of an mHealth intervention in enhancing adherence to lifestyle practices, increasing knowledge on prehypertension and hypertension, and reducing blood pressure among participants in the experimental and control groups.

**Methods:**

The study consists of 2 phases. Phase 1 used a cross-sectional survey design, and phase 2 included a pragmatic randomized controlled trial with cluster randomization. The protocol was prepared according to the SPIRIT (Standard Protocol Items: Recommendations for Interventional Trials) 2013 checklist. The CONSORT (Consolidated Standards of Reporting Trials of Nonpharmacologic Interventions) 2017 guideline was followed for reporting the protocol. The estimated sample size for phase 1 was 762 participants, and the sample size for the phase 2 was 85 participants per group. Both the control and experimental groups will receive education on prehypertension and hypertension, with the experimental group additionally receiving an mHealth app. The experimental group’s adherence to lifestyle practices will be monitored every 15 days, and reminder messages will be sent to nonresponders. Both groups will be followed up with on-site after 1, 3, and 6 months to assess their knowledge on prehypertension and hypertension, blood pressure, and lifestyle practices. The primary outcome of the study will be an improvement in blood pressure readings. The secondary outcomes will include adherence to lifestyle practices and knowledge on prehypertension and hypertension.

**Results:**

This study was funded by the Indian Council of Medical Research (grant 2021-11792, received February 2023). The study is ongoing. Phase 1 was completed on March 29, 2024, with data collected from 762 samples from 8 randomly selected colleges from Udupi District. Currently, phase 2 is in progress. The data will be analyzed using jamovi software (version 2.3.21; The jamovi project). Phase 1 and 2 findings will be analyzed and the results will be published in a peer-reviewed journal. Ethical approval for the study was obtained in May 2022 (160/2022).

**Conclusions:**

Identifying high-risk groups of young adults with prehypertension enables early interventions to prevent future hypertension and combat the cardiovascular burden globally. The mHealth intervention is considered to be an effective strategy to impart knowledge and promote healthy behaviors among young adults. The study will contribute to achieving the United Nation’s Sustainable Development Goal 3, which focuses on ensuring good health and well-being.

**Trial Registration:**

Clinical Trial Registry of India CTRI/2023/04/051784; https://tinyurl.com/57y9enyd

**International Registered Report Identifier (IRRID):**

DERR1-10.2196/67216

## Introduction

Hypertension is the third most significant risk factor contributing to the burden of noncommunicable diseases (NCDs) and places a considerable public health burden on cardiovascular health in India [1]. According to the World Health Organization, hypertension is a leading cause of premature death, with prehypertension serving as a critical precursor to hypertension both nationally and globally [2]. The seventh report of the Joint National Committee classifies prehypertension as a systolic blood pressure of 120-139 mmHg or a diastolic blood pressure of 80-89 mmHg [3]. However, the eighth report of the Joint National Committee guidelines do not define prehypertension because their recommendations focus on individuals with diagnosed hypertension [4]. Despite the rising prevalence, increased awareness, and availability of treatments, hypertension remains poorly controlled, particularly in low-income and middle-income countries, leading to major cardiovascular events [2].

A study conducted in India revealed that the prevalence of hypertension and prehypertension among young adults is 11.2% and 33.3%, respectively [5]. Individuals with a family history of hypertension and those who are physically inactive have a higher risk of hypertension [6]. Identifying prehypertension during its asymptomatic stage allows for timely interventions to normalize blood pressure, thereby preventing or delaying the onset of hypertension [7].

Many young adults with increased blood pressure remain undiagnosed, and a substantial proportion of individuals are unaware of their existing prehypertension. Young people are one of India’s most valuable resources. Studies in India reported the prevalence of prehypertension among young adults to be in the range 24.6%-65% [5,7-13].

Mobile devices have become integral to health care, providing easy access to health information both at home and on the go [14]. Early identification of prehypertension enables proactive blood pressure management through preventive strategies, thereby reducing cardiovascular morbidity and mortality.

Globally, hypertension is the leading cause of death, accounting for 10.4 million deaths annually [15]. Prehypertension, the initial stage of hypertension, represents a critical point for intervention where appropriate measures can delay or prevent the progression to hypertension. In addition, prehypertension is associated with an increased risk of both hypertension and cardiovascular diseases (CVDs) [16].

A study conducted in the coastal villages of Udupi District in Southern India found that the prevalence of prehypertension among young adults (aged 20-30 years) was 45.2%. Biological factors, such as being in the 25- to 30-year age group, having preobesity or obesity, and behavioral factors, including sedentary occupations and excessive salt intake, were found to be associated with prehypertension [7].

Globally, CVDs account for approximately 17.9 million deaths among middle-aged adults, with hypertension being the most common cardiovascular disorder, responsible for 20%-50% of all CVD-related deaths. Once considered a condition mainly affecting adults, hypertension is now increasingly prevalent among younger populations, with its onset reported even in childhood [6,17].

Studies have reported a high prevalence of hypertension among Indian adults, with nearly 1 in 3 individuals having this condition. With approximately 762 million adults aged 18 years and older in India, this equates to an estimated 234 million adults with hypertension, indicating a significant future increase in the CVD burden. This finding highlights the urgent need for early detection and treatment because effective blood pressure control can prevent nearly one third of all cardiovascular-related deaths [15]. In addition to blood pressure management, therapeutic strategies should include modifying lifestyle, managing weight, and addressing other risk factors to reduce residual cardiovascular risk [18,19].

Health education within the community is vital to increase awareness about hypertension and its risk factors among younger generations. Promoting physical activity and healthy eating is critical to counter the rapid rise of NCDs in many low-income and middle-income countries. Leveraging modern information and communication technologies to deliver interventions for physical activity and dietary changes is particularly promising, given the increasing availability of these technologies in such regions [17].

The prevalence of prehypertension among adolescents is rising, though it remains underreported. This condition often progresses to hypertension in adulthood, with young adults experiencing cardiovascular and cerebrovascular disorders before the age of 40 or 45 years. This leads to significant morbidity and mortality and a substantial socioeconomic burden on society [6,20].

The conceptual framework adopted in this study is modified from the predisposing, reinforcing, and enabling constructs in educational/environmental diagnosis and evaluation (PRECEDE)-policy, regulatory, and organizational constructs in educational and environmental development (PROCEED) model [21,22] developed by Green and Kreuter [23] (Figure 1). Predisposing factors in the PRECEDE-PROCEED framework include antecedents to behavior, such as demographic and clinical factors, knowledge, and lifestyle behaviors. The enabling factors include existing knowledge on prehypertension and hypertension, lifestyle practices, and annual family income. The reinforcing factors include a family history of hypertension that encourages prompt health maintenance. The intervening variables are the on-site awareness program and the mobile health (mHealth) app aimed at enhancing knowledge on prehypertension and hypertension as well as adherence to healthy lifestyle practices. The outcome variables include blood pressure, knowledge on prehypertension and hypertension, and lifestyle practices.

**Figure 1 figure1:**
[figure not shown]
Conceptual framework on mHealth interventions for prehypertension among young adults based on the PRECEDE-PROCEED model developed by Green and Kreuter [23]. mHealth: mobile health; PRECEDE: predisposing, reinforcing, and enabling constructs in educational/environmental diagnosis and evaluation; PROCEED: policy, regulatory, and organizational constructs in educational and environmental development.

Given the severity of this problem, the present study aims to determine the prevalence of prehypertension and evaluate the effect of mHealth interventions on adherence to lifestyle practices, knowledge on prehypertension and hypertension, and blood pressure among young adults. The growing adolescent population in India and the increasing risk factors highlight the importance of primary prevention as a crucial strategy to combat this epidemic.

This study aims to contribute to the United Nation’s Sustainable Development Goal 3 ensuring healthy lives and promoting well-being for all at all ages. The specific target is to reduce premature mortality from NCDs by one third through prevention and treatment and promote mental health and well-being by 2030.

## Methods

### Study Design

#### Overview

The study is designed to be carried out in 2 phases. A cross-sectional survey design was used in phase 1. Because the study aims to evaluate the effect of the mHealth program on adherence to lifestyle practices, knowledge of prehypertension, and blood pressure, a pragmatic randomized controlled trial with cluster randomization was implemented in phase 2. The protocol follows the SPIRIT (Standard Protocol Items: Recommendations for Interventional Trials) 2013 checklist [24], which is provided in Multimedia Appendix 1. The CONSORT (Consolidated Standards of Reporting Trials of Nonpharmacologic Interventions) 2017 flowchart of the study is presented in Figure 2 [25-28].

**Figure 2 figure2:**
[figure not shown]
CONSORT (Consolidated Standards of Reporting Trials of Nonpharmacologic Interventions) 2017 flow diagram for the study. N denotes the number of colleges (ie, clusters) and n denotes the number of participants per cluster. DASH: dietary approach to stop hypertension.

#### Phase 1

After obtaining administrative permission from the Institutional Research Committee, Institutional Ethical Committee, and Joint Director of Collegiate Education, Udupi District, taluks from Udupi District were randomly selected to collect data for assessing the prevalence of prehypertension in phase 1. The data were collected on-site from young adults of colleges from randomly selected taluks. Baseline information, clinical variables, lifestyle practices, knowledge on prehypertension and hypertension, and blood pressure were measured for all participants from the selected colleges. An automated, digital, oscillometric blood pressure machine (Omron) was used to measure blood pressure after device calibration. As of March 29, 2024, phase 1 was completed with data collected from 762 samples from 8 randomly selected colleges.

#### Phase 2

Colleges with students having prehypertension identified during phase 1 were considered as clusters (N=6) and will be allocated to the intervention (N=3) and control groups (N=3) by simple randomization using the chit method. A random allocation sequence using the chit method was generated by research assistants who are not involved in the study. Currently, phase 2 is in progress.

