### Data Collection Procedure and Instruments

The baseline data will be collected using a tool with 2 sections: demographic and clinical parameters. Adherence to lifestyle practices will be assessed using the adherence scale on lifestyle practices developed by the researchers, with a maximum score of 12. Adherence will be categorized as “adherent” for those achieving ≥80% (a score of ≥10) and “nonadherent” for those scoring <80% (a score of <10). A structured knowledge questionnaire on prehypertension and hypertension will be used to assess knowledge on the subject. The questionnaire consists of 30 items, with a maximum score of 30. The items are based on the Joint National Committee 7 recommendations for nonpharmacological interventions in the management of prehypertension. Knowledge levels will be classified as poor (a score of 0-9), average (a score of 10-20), or good (a score of 21-30). Blood pressure will be assessed using a digital blood pressure apparatus. The baseline blood pressure will be measured after a 5-minute to 10-minute rest period. Two readings will be taken 1-3 minutes apart, and the average will be calculated. In case of a difference of more than 5 mmHg between the 2 readings, an additional 2 readings will be obtained, and the average of these multiple readings will be used [32]. Prehypertension will be identified among young adults based on the average of 2 blood pressure readings. The same procedure will be followed during the follow-up sessions at 1, 3, and 6 months. A calibrated stadiometer and weighing machine will be used to assess the heights and weights of the participants.

The validated tools were tested for reliability on 20 students from the selected degree colleges in Udupi District. The reliability of the structured knowledge questionnaire was assessed using the split-half method (*r*=0.911). The tools were pretested with 10 students from a degree college in Udupi District. A pilot study was conducted with 20 students at a selected degree college.

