## Results

Ethical approval was obtained on May 11, 2022 (IEC1 160/2022), and the Indian Council of Medical Research provided funding for this project on February 9, 2023 (Project ID:2021-11792). The project is still in progress. On March 29, 2024, phase 1 was completed, with data gathered from 762 samples from 8 randomly chosen colleges in the Udupi District. Phase 2 is now underway (Table 2). The outcomes of phase 1 and phase 2 will be published in reputable peer-reviewed journals.

**Table 2 table2:** Progress of phase 2 detailing the timelines of sample assessment.

Time	Baseline	1 month	3 months	6 months
Intervention group	September 16 to November 19, 2024	October 16 to December 20, 2024	January 2 to February 28, 2025	Started on April 4, 2025, and is expected to be completed by June 30, 2025
Control group	September 19 to October 19, 2024	October 30 to November 29, 2024	January 2 to February 28, 2025	Started on April 4, 2025, and is expected to be completed by June 30, 2025

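### Phase 2 entry rests on one phase 1 visit at least 171 days before baseline and is not stated to be re-checked, so the population label needs correcting and baseline blood pressure category should be reported by arm

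*Protocol article*

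**What the plan says.** **Entry.** The phase 2 criteria in the inclusion and exclusion textbox (Methods, Study Participants and Sampling) admit students found prehypertensive in phase 1. The hypertension exclusion also refers to the phase 1 finding.

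**Timing.** Methods, Study Design, Phase 1 states: "As of March 29, 2024, phase 1 was completed with data collected from 762 samples from 8 randomly selected colleges". Table 2 in Results gives the phase 2 baseline as "September 16 to November 19, 2024" for the intervention group and "September 19 to October 19, 2024" for the control group.

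**Classification.** The Introduction cites a guideline that "classifies prehypertension as a systolic blood pressure of 120-139 mmHg or a diastolic blood pressure of 80-89 mmHg". Data Collection Procedure and Instruments says "Prehypertension will be identified among young adults based on the average of 2 blood pressure readings". The readings are taken 1-3 minutes apart. If they differ by more than 5 mmHg, "an additional 2 readings will be obtained, and the average of these multiple readings will be used". The value is therefore the mean of 2 to 4 readings from one visit. On later visits it says: "The same procedure will be followed during the follow-up sessions at 1, 3, and 6 months".

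**Population named.** The title speaks of "Reducing Blood Pressure Among Young Adults With Prehypertension".

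**The concern.** Day-to-day variation in blood pressure is not averaged out by readings taken minutes apart. When people are selected because one visit fell in a range, their mean moves back towards the population mean at the next visit, and some leave the range in either direction. Here the next visit is the phase 2 baseline, about six to eight months later.

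Three things follow:

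- Participants in the normal range at baseline are reported as having prehypertension, so the conclusion is attached to a population that was not quite the one studied.
- Such participants may have less room for a fall in blood pressure, which may dilute the measured effect.
- Some participants may be in the hypertensive range at baseline, although the criteria show that hypertensive students were meant to be left out. The article does not say whether the phase 1 finding or the baseline value governs. The two need to be reconciled.

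**Working it through.** **1. The plan's own figures.** Phase 1 size: 1.96² × 0.45 × 0.55 / 0.05² = 380.3, rounded up to 381; 381 × 2 = 762, as stated. Phase 2: 34 / 0.8 = 42.5; 42.5 × 2 = 85 per group, so 170 in all. The base figure of 34 cannot be checked, because the detectable difference and the correlation are not given.

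**2. The gap.** The last possible phase 1 date is 29 March 2024.

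| Arm | First baseline | Last baseline | Days from 29 March |
|---|---|---|---|
| Intervention | 16 Sep 2024 | 19 Nov 2024 | 171 to 235 |
| Control | 19 Sep 2024 | 19 Oct 2024 | 174 to 204 |

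These are minimum gaps. Anyone measured before 29 March waited longer.

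**3. Share outside the range at baseline (illustration).** The article gives no blood pressure mean, SD or between-visit correlation r, so all of these are assumed: mean systolic 115-118 mmHg (SD 11-12), mean diastolic 73-75 mmHg (SD 8), systolic-diastolic correlation 0.6, bivariate normal, two visits. A visit is hypertensive at ≥140 or ≥90 mmHg, normal below 120 and below 80, and otherwise prehypertensive. Simulated phase 1 prevalence of prehypertension is then 36-45%, close to the 45% used for phase 1. Two of the scenarios, among those prehypertensive at the first visit:

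| Assumed mean (SD) | r | Normal | Hypertensive | Total out of range |
|---|---|---|---|---|
| 116 (11) / 74 (8) | 0.5 | 41.0% | 5.3% | 46.3% |
| 116 (11) / 74 (8) | 0.8 | 26.4% | 4.6% | 31.0% |
| 118 (11) / 75 (8) | 0.5 | 36.3% | 6.5% | 42.8% |
| 118 (11) / 75 (8) | 0.8 | 23.4% | 5.3% | 28.7% |

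Over all these inputs, about 24-44% of those enrolled are normal at baseline, 4-8% are hypertensive, and about 30-48% are out of range in total.

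**4. Second model, using prevalences in the article.** One latent variable with 45% prehypertension (Study Participants and Sampling) and 11.2% hypertension (Introduction) gives:

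- r = 0.5: 33.3% normal + 13.3% hypertensive = 46.6%
- r = 0.8: 22.2% + 10.3% = 32.5%
- r = 0.9: 15.8% + 7.5% = 23.3%

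The total agrees with step 3, but the split does not. The step 3 inputs imply only 2.6-5.5% hypertension in phase 1, against the cited 11.2%.

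**5. Outer range.** The Introduction cites prehypertension prevalences of 24.6-65%. With 65% prehypertension, 11.2% hypertension and r = 0.9, 13.7% are out of range. With 24.6%, an assumed 5% hypertension and r = 0.4, 64.9% are. Hence about 14-65%.

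**6. Where the regression to the mean falls.** The expected fall between phase 1 and baseline is (1 − r) × (mean of those selected − population mean). In the 118/75 scenario at r = 0.5 the fall is 3.56 mmHg, so the excess is 3.56 / 0.5 = 7.1 mmHg. At r = 0.8 this predicts 0.2 × 7.1 = 1.42 mmHg, as simulated. This fall is complete before the phase 2 baseline. With three equally correlated visits, untreated drift from baseline to follow-up is about 0 in all enrolled. In the subset whose baseline confirms prehypertension it is 0.9-3.4 mmHg (systolic SD 11, r = 0.8 to 0.5), because that subset is selected again on the baseline value.

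**7. Use of the phase 1 reading.** Under the step 3 inputs, adding phase 1 systolic pressure to a model that already adjusts for the phase 2 baseline cuts the participant-level residual variance by about 5-13%.

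**The case against.** **The re-check may exist.** The article does not say that the range was left unapplied at baseline; it is silent. The sentence on identifying prehypertension stands next to the description of baseline measurement and could be read as classifying at each session. The flow diagram is not shown, and an article may leave such a step to the full protocol. This stands as far as it goes, and a single sentence confirming the re-check would settle the labelling. But the criteria that are printed name phase 1, and the sentence on follow-up visits concerns how blood pressure is measured, not who stays eligible.

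**One visit is no better than another.** Being normal at baseline is not proof of being free of prehypertension. Under the same assumptions, 43-50% of those normal at baseline are at or above 120/80 mmHg again at a third visit. This stands: the shares above describe category at a visit, not true status.

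**Screening-based entry is ordinary in a pragmatic trial.** Agreed. The objection is to the label, not to the choice.

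**Stronger readings that do not hold.** A reader might infer that regression to the mean will produce a spurious treatment effect. It will not in the between-arm contrast, because entry is by the same rule in both arms and both have a new baseline after selection. A reader might also turn the dilution into a loss of power. That needs an effect size in normotensive participants, which the article does not give, and a power figure that can be checked for blood pressure. The phase 2 calculation is instead based on an SD attributed to the prevalence of prehypertension.

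**Conclusion.** The point holds as one of labelling, reporting and unused information, not of bias. It is exact that entry and the hypertension exclusion refer to one phase 1 visit, that this visit was at least 171 days before baseline, and that the text states no re-check.

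The number of participants affected is not known from the article. About 30-48% out of range is an illustration that rests on the assumed means, SDs and a between-visit correlation of 0.5-0.8. About 14-65% is the range over wider assumptions, and the split between normal and hypertensive is less certain than the total. Neither range should be quoted as a finding about this trial; the recorded baseline data will give the actual count. Dilution of the effect is possible, but its size cannot be derived from the documents.

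**What to change.** 1. Describe the analysed population as *prehypertension at phase 1 screening* in the analysis plan and report. If the range was in fact applied again at the phase 2 baseline, say so instead.
2. Report by arm how many participants were normal, prehypertensive and hypertensive at the phase 2 baseline.
3. Add the phase 1 blood pressure, which was taken before allocation, as a covariate alongside the phase 2 baseline in the between-arm model. The 5-13% reduction is in participant-level variance. With six colleges, the gain in precision of the arm contrast may be smaller.
4. Keep the comparison of all enrolled participants primary, and do not let baseline category become a ground for removal from it. A comparison in baseline-confirmed participants is optional. If wanted, pre-specify it as a sensitivity analysis of the between-arm contrast only, since within-arm change in that subset carries the drift shown in step 6.

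**Cost.** Wording, one table and one covariate, all from data already recorded. No change to enrolment or measurement is needed. The optional subset would hold about 170 × 0.52 = 88 to 170 × 0.70 = 119 participants under the 30-48% illustration, so its interval would be wider, and this should be stated with the result.

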#### Study Participants and Sampling

The study will be conducted in the Udupi District of Karnataka, which is divided into 7 taluks (Udupi, Kundapur, Karkala, Hebri, Byndoor, Brahmavar, and Kapu). There are 33 private and 10 government-run colleges in the district. Young adults aged 18-25 years working toward a bachelor of science, bachelor of communication, or bachelor of arts in colleges in Udupi District who meet the inclusion and exclusion criteria (Textbox 1) will be considered for the study.

Inclusion and exclusion criteria for the study.

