**Phase 2**
Inclusion criteriaYoung adults identified to have prehypertension in phase 1.Young adults with prehypertension willing to participate in the study.Young adults with prehypertension having android mobile phones.Colleges with students having prehypertension identified during phase 1 were considered.Exclusion criteriaYoung adults identified to have hypertension in phase 1 and who were already diagnosed with other systemic disorders.Young adults with prehypertension who are on medications for any other ailments.Young adults with prehypertension who do not have android mobile phones.

The calculated sample size for phase 1 was determined to be 381 participants using the following formula for estimating a proportion, where n is the sample size required, Z_1-α/2_ is the desired confidence level (ie, for a 95% confidence level, Z_1-α/2_=1.96), P is the prevalence, and d is the margin of error:

This calculation assumes the prevalence of prehypertension among young adults to be 45% at a 95% confidence level with a 5% margin of error (absolute precision) based on a previous study by Kini et al [7]. After multiplying by a design effect of 2 due to cluster sampling, the sample size was determined to be 762 participants.

The sample size for phase 2 was 34 participants per group, considering a 38% anticipated population SD of the primary outcome variable (ie, the prevalence of prehypertension) obtained using the equation for repeated measures ANOVA given below. In the equation, n is the sample size required, Z_1-α/2_ is the desired confidence level (ie, for a 95% confidence level, Z_1-α/2_=1.96), Z_1-β_ is the power of the test (ie, for a power of 80%, Z_1-β_=0.84), σ² is the population variance (ie, square of the SD), m is the number of groups being compared, ρ is the correlation coefficient between groups, and d is the minimum detectable difference.

Accounting for a 20% dropout rate, the final sample size was 43 participants per group. After multiplying by a design effect of 2 due to cluster randomization, the sample size was determined to be 85 participants per group.

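### The six colleges were drawn 3:3 without using the phase 1 data to balance them, and the planned analysis does not adjust for the chance baseline difference that this allows

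*Protocol article*

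**What the plan says.** The Phase 2 part of the Study Design section takes six colleges in which phase 1 found prehypertensive students. They "will be allocated to the intervention (N=3) and control groups (N=3) by simple randomization using the chit method". It mentions no stratification, pairing or balance criterion. It adds that research assistants outside the study have generated the sequence.

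The Phase 1 part shows what was already held: "Baseline information, clinical variables, lifestyle practices, knowledge on prehypertension and hypertension, and blood pressure were measured for all participants from the selected colleges". It also says that "phase 1 was completed with data collected from 762 samples from 8 randomly selected colleges", by March 29, 2024. Phase 2 participants are the students found prehypertensive in that survey (Textbox 1), so their numbers and readings were available by college before the draw.

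The Abstract states that "the sample size for the phase 2 was 85 participants per group". Study Participants and Sampling derives this with a design effect of 2. The Statistical Analysis section plans a per-protocol repeated measures ANOVA over baseline, 1, 3 and 6 months, and mentions neither a baseline covariate nor a college term. Table 2 dates the baseline assessments from September 16 to November 19, 2024.

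**The concern.** Randomisation balances arms on average over many units. With three colleges per arm, a single draw can leave the arms visibly apart on the primary outcome before the intervention starts. Most cluster trials have no outcome data at the time of allocation. This one did, and the stated draw does not use them.

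What is at stake is precision and credibility. If the arms start apart, a reader of the final report has to judge how much of the follow-up difference was there at the outset. Taking baseline as one more outcome time point does not remove that difference efficiently; using it as a covariate does.

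There is also a wording problem. Simple randomisation means independent draws, which is not what a fixed three-and-three split is.

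**Working it through.** **Reproducing the plan's figure.** Inputs from Study Participants and Sampling: 34 per group, 20% dropout, design effect 2.
- 34 / 0.8 = 42.5; 42.5 × 2 = 85 per group. (Doubling the rounded 43 would give 86.)
- Three colleges per arm: 85 / 3 = 28.3 students per college.

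**Implied intracluster correlation.** (2 − 1) / (28.3 − 1) = 0.037. The article does not state this value; it follows from the design effect.

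**Chance difference in mean baseline blood pressure, equal college sizes.**
- Variance of a college mean: 0.0366 + 0.9634 / 28.33 = 0.0706 student variances.
- SD of the difference between arms: √(2 × 0.0706 / 3) = 0.217 student SDs. Equivalently, √(2 × 2 / 85) = 0.217.
- P(|difference| > 0.25 SD): 0.25 / 0.217 = 1.15, two-sided 25%. For 0.30 SD it is 17%.

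The article gives no SD in mmHg, so the result stays in SD units.

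**What balancing could have done.** There are C(6,3) = 20 allocations. A simulation of 40,000 trials compared an open 3:3 draw with a draw from the 10 allocations best balanced on blood pressure and arm size jointly. The coefficient of variation (CV) of college size is an assumption, because the text gives no college sizes. ICC is 0.037.

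| Size CV | Draw | SD of difference | P(>0.25 SD) | P(smaller arm <68 of 170) |
|---|---|---|---|---|
| 0.3 | open 3:3 | 0.22 | 26% | 10% |
| 0.3 | best 10 of 20 | 0.15 | 9% | 1% |
| 0.5 | open 3:3 | 0.23 | 27% | 32% |
| 0.5 | best 10 of 20 | 0.15 | 10% | 14% |

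Over ICC 0.01 to 0.10 and these two CVs, the SD is 0.18 to 0.32 for the open draw and 0.12 to 0.21 for the balanced one. The direction does not depend on the assumptions. The calculation takes the phase 1 college means to equal the trial baseline means.

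**Cost of an uneven split.** At 68 against 102, the standard error relative to 85 against 85 is √[(1/68 + 1/102) / (2/85)] = √1.042 = 1.021, an increase of about 2%.

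**Why the form of the analysis matters.** Let r be the correlation of baseline with follow-up (not given; taken as 0.3 to 0.7) and D the chance baseline difference. With no treatment effect, the expected follow-up difference is rD. The contrast in change from baseline is then off by (1 − r)D. For D = 0.25 SD this is 0.7 × 0.25 = 0.175 SD at r = 0.3 and 0.3 × 0.25 = 0.075 SD at r = 0.7. Baseline as a covariate removes this. For a single follow-up, ignoring clustering, its variance relative to the change contrast is (1 − r²) / [2(1 − r)] = (1 + r) / 2, that is 0.65 to 0.85.

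**The label.** Six independent fair draws give 3:3 with probability 20 / 64 = 31%. The stated split is fixed, so it is a restricted draw.

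**The case against.** The case on the other side is substantial.

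- *An open 3:3 draw is legitimate.* This stands: it is valid and unbiased in expectation. Balancing also has a price. The smallest two-sided permutation p-value is 2/20 = 0.10 with all 20 allocations and 2/10 = 0.20 with 10. With six clusters, keeping all 20 is a defensible choice.
- *Phase 1 data are an imperfect guide.* This stands. Phase 1 ended in March 2024 and baseline began in September. If college means at the two times correlate at only 0.6 (an assumption), constraining on blood pressure alone takes the SD from 0.22 to just 0.18. Final numbers also depend on willingness and on "Young adults with prehypertension having android mobile phones", so eligible counts were known only approximately.
- *Arm size hardly matters.* This largely stands: about 2% on the standard error at 68 against 102. Unequal colleges are not shown either. At the planned 45% prevalence, 762 / 8 × 0.45 is about 43 prehypertensive students per college against 28 needed, so a quota per college was feasible. The flow diagram that might settle it is not visible here.
- *Baseline is already in the ANOVA, and covariates may be settled in an analysis plan that is not shown.* In part. A baseline difference does not pass one for one into the group-by-time effect, and the 0.22 SD is not an error in the treatment effect. But the article does commit to baseline as an outcome time point, and that is the feature to change.

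A reader might go further and infer that the imbalance is confounded with arm and beyond repair by modelling. The documents do not support that: baseline blood pressure is measured in every participant and can be adjusted for. Nor can one infer that college type is likely to be unbalanced. "There are 33 private and 10 government-run colleges in the district", but that describes the district, and nothing says which type the six trial colleges are.

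**Conclusion.** The point holds as a modest one. The protocol allocated six colleges without using blood pressure data it already had. Its own design effect implies a chance baseline difference with an SD of about 0.22 student SDs, above 0.25 SD in about one draw in four. That figure rests only on the stated design effect, the 85 per group and equal college sizes. The reduction to about 0.15 rests in addition on an assumed size CV of 0.3 to 0.5 and on phase 1 means tracking trial baseline means.

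It would be wrong to conclude that the trial is biased by design or that the arms are in fact unbalanced: no college-level results are given. It would also be wrong to ask for a new draw. The sequence has been generated and baseline assessment ended in November 2024. What remains open is the analysis and the reporting, where the improvement is nearly free.

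**What to change.** 1. **Statistical Analysis.** Analyse the 1-, 3- and 6-month blood pressure as outcomes, with each participant's baseline (or phase 1) blood pressure as a prespecified covariate, in an analysis that accounts for college. With six colleges only 6 − 2 = 4 between-college degrees of freedom are available, so do not add a list of college-level covariates.
2. **Reporting.** Tabulate phase 1 blood pressure and the number of prehypertensive students by college and arm, so that readers can see what the draw produced.
3. **Study Design, Phase 2.** Describe the draw as a fixed 3:3 allocation of six colleges by lot instead of simple randomisation, and use one tense for a step that has been completed.

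Cost: one covariate, one table and a sentence of rewording. No extra participants, visits or measurements are needed. The change should be dated and made before outcome data are compared by arm.
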